# RObotic-Assisted Rehabilitation for balance and gait in Stroke patients (ROAR-S): study protocol for a preliminary randomized controlled trial

**DOI:** 10.1186/s13063-022-06812-w

**Published:** 2022-10-12

**Keywords:** Older adults, Elderly, Rehabilitation, Falls, Technology

## Abstract

**Background:**

Stroke, the incidence of which increases with age, has a negative impact on motor and cognitive performance, quality of life, and the independence of the person and his or her family, leading to a number of direct and indirect costs. Motor recovery is essential, especially in elderly patients, to enable the patient to be independent in activities of daily living and to prevent falls. Several studies have shown how robotic training associated with physical therapy influenced functional and motor outcomes of walking after stroke by improving endurance and walking strategies.

Considering data from previous studies and patients’ needs in gait and balance control, we hypothesized that robot-assisted balance treatment associated with physical therapy may be more effective than usual therapy performed by a physical therapist in terms of improving static, dynamic balance and gait, on fatigue and cognitive performance.

**Methods:**

This is an interventional, single-blinded, preliminary randomized control trial. Twenty-four patients of both sexes will be recruited, evaluated, and treated at the UOC Rehabilitation and Physical Medicine, Fondazione Policlinico Universitario A. Gemelli IRCCS in Rome from January to December 2022. Patients will be randomized into two groups: the experimental group will perform specific rehabilitation for balance disorder using the Hunova® robotic platform (Movendo Technology srl, Genoa, IT) for 3 times a week, for 4 weeks (12 total sessions), and for 45 min of treatment, in addition to conventional treatment, while the conventional group (GC) will perform only conventional treatment as per daily routine. All patients will undergo clinical and instrumental evaluation at the beginning and end of the 4 weeks of treatment.

**Conclusions:**

The study aims to evaluate the improvement in balance, fatigue, quality of life, and motor and cognitive performance after combined conventional and robotic balance treatment with Hunova® (Movendo Technology srl, Genoa, IT) compared with conventional therapy alone. Robotic assessment to identify the most appropriate and individualized rehabilitation treatment may allow reducing disability and improving quality of life in the frail population. This would reduce direct and indirect social costs of care and treatment for the National Health Service and caregivers.

**Trial registration:**

ClinicalTrials.gov NCT05280587. Registered on March 15, 2022.

**Supplementary Information:**

The online version contains supplementary material available at 10.1186/s13063-022-06812-w.

## Background and rationale

Stroke represents the second leading cause of disability worldwide; its incidence increases with age and around 25% of stroke affected people over 65 years old [1]. Stroke consequences, especially in older adults, affected one or more activities of daily living [2] and largely affect the quality of life and independence of the person and of his/her family. Moreover, stoke outcomes imply large direct and indirect social costs [3].

Motor recovery is essential in patients with stoke outcome [4, 5]; especially in older adults, a recovery of smoother, safer, and more correct walking is an essential requirement to allow the patient to be autonomous in the activities of daily living; trunk control and lower limb motor control are an essential outcome in stroke rehabilitation to prevent falls [6–8]. This is particularly important in this fragile population characterized by multimorbidity, polymedication, and nutritional deficit [9–11]. Several studies and a recent meta-analysis have shown how robotic training associated with physical therapy has influenced functional and motor gait and cognitive outcome after stroke, improving endurance and walking strategies [12–15]. In addition, frequently, stroke causes an impairment of the cognitive function that could affect the deterioration of balance and gait during dual-task activities; the study of these processes can be of interest for rehabilitation purposes [16–20]. Also important in rehabilitation are the motor and cognitive substrates that characterize each patient, which can positively influence the recovery process [21–23].

Considering data of the previous study and patients’ needs in the control of walking and balance, we have hypothesized a robotic-assisted balance treatment associated with physical therapy may be more effective than usual therapy performed by a physical therapist. Therefore, the present study aims to evaluate the effects of technological rehabilitation utilizing a robotic balance platform in terms of improvement in static, dynamic balance, and ambulation (assessed with clinical scales and instrumental measures) on fatigue and cognitive performance (attention, dual-task cost and cognitive-motor interference and on quality of life).

### Objective

The present study aims to evaluate the effects of a technological rehabilitation treatment and to assess fatigue and cognitive performance of treated patients.

### Trial design

The present study is an interventional, single-blinded, non-inferiority, randomized control pilot trial. The study protocol follows the Standard Protocol Items: Recommendations for Interventional Trial (SPIRIT) checklist (Additional file 1). The study registration data are shown in Table 1.

## Methods

### Study setting

The trial will be carried out at the Rehabilitation and Physical Medicine Unit of the Fondazione Policlinico Universitario A. Gemelli IRCCS in Rome from February 2022 to January 2023. It will include older adults with stroke outcomes of both sexes, who will be divided into two groups by randomization (Fig. 1): one experimental group (Hunova group, HuG) will perform specific rehabilitation for the balance disorder using the robotic platform Hunova® (Movendo Technology srl, Genova, IT; Fig. 2) 3 times a week, for 4 weeks (12 sessions), with each treatment lasting 45 min, in addition to the conventional treatment, and one group will perform only the conventional treatment (conventional group, CoG), as per daily routine, as described later. Figure 3 shows the study flowchart.

**Fig. 1 Fig1:**
[figure not shown]
Study design with Group randomization

**Fig. 2 Fig2:**
[figure not shown]
Robotic platform Hunova® (Movendo Technology srl, Genova, Italy) in our laboratory

**Fig. 3 Fig3:**
[figure not shown]
The study flowchart

### Eligibility criteria

Elderly patients (age > 65 years) with ischemic or hemorrhagic stroke outcomes documented through neuroimaging techniques (magnetic resonance imaging or computed tomography) that occurred between 1 and 6 months previously will be included in the study, who have sufficient cognitive abilities to execute simple orders and to understand the physical therapist’s instructions as assessed through the Token Test (score ≥ 26. 5), who are able to walk independently or with minimal assistance, and who are able to understand and sign informed consent.

Patients with systemic, neurological, or cardiac pathologies that make ambulation risky or cause motor deficits, orthopedic or postural problems, plantar ulcers, and partial or total amputation of foot segments will be excluded.

### Who will take informed consent

Investigators participating in the study, through a comprehension test (see eligibility criteria), will screen patients to assess their inclusion in the study.

Participation in the study is voluntary: each patient will receive explicit information about the nature of the project and must sign a written consent before being included. Participants may withdraw consent to participate at any time without consequence.

In the event that the patient is not fully able to give informed consent due to disease characteristics, the family caregiver will be involved in the information and consent process along with the patient. Finally, researchers will collect signed informed consent, as required by the Ethics Committee.

### Assessment and intervention

#### Assessment

All participants declared eligible for the study will be evaluated at baseline (T0) and at the end of 4 weeks of treatment (T1).

At T0, researchers will collect demographical and clinical information of enrolled patients, such as age, sex, schooling, comorbidity, date of the event, etiology of the event, latency from the event, and pharmacological therapies in place. In addition, information on motor reserve, using the Lifetime Total Physical Activity questionnaire (LTPAq), and cognitive reserve, using the Cognitive Reserve Index questionnaire (CRIq), will be collected.

In addition to this, clinical and instrumental assessments will be conducted at both T0 and T1. Clinical assessment will be performed using the following rating scales: (i) Motricity Index Lower Limb (MI-LL) [24], Berg Balance Scale (BBS) [25], Time Up & Go (TUG) [26], and Short Physical Performance Battery (SPPB) [27] will be used to assess motor performance and balance; (ii) Ambulation Index (AI) [28], Walking Handicap Scale (WHS) [29], Functional Ambulation Classification (FAC) [30], the 10-Meter Walking Test (10MWT) [31], and 6-Minute Walking Test (6MWT) [32] will be used to assess ambulation performance; (iii) Modified Barthel Index (BIM) [33] and EuroQoL5D (EQ-5D) [34] will be used to assess autonomy and quality of life; (iv) Modified Fatigue Impact Scale (MFIS) [35] and Fatigue Scale for Motor and Cognitive Function (FSMC) [36] will be used to assess fatigue; (v) Frontal Assessment Battery (FAB) [37], Stroop Color Word Test (SCWT) [38], Symbol Digit Modalities Test (SDMT) [39], Digit Cancellation Test (DCT) [40], and Trail Making Test (TMT) [39] will be used to assess cognitive performance.

Instrumental assessment will include balance and gait analysis. Balance assessment will be carried out using the robotic platform (Hunova®, Movendo Technology srl, Genova, IT) and will be performed in static, dynamic, and dual-task conditions (i.e., during the execution of a concurrent cognitive task—the SCWT), both in sitting and standing positions. Posturography data will be obtained from the analysis of the trajectories of the center of pressure (CoP). Then, from the instantaneous CoP positions, we will obtain the following variables related to the balance performance: speed of the oscillations of the CoP along the anteroposterior (AP) and mid-lateral (ML) axes, length of the CoP trajectory, area of the 95% confidence ellipse, and Romberg Test [the ratio of the value of the length in the closed eyes (CE) condition and the same value in the open eyes condition (OE)].

Gait analysis will be performed using the Smart D500 stereo-photogrammetric system composed of 8 cameras, placing 22 markers on anatomical landmarks, according to as established by the Davis. The evaluation will involve the acquisition of 10 walking trials. Alongside a physical therapist, the patient will walk barefoot along a path of approximately 6 m at his/her natural speed. Before the actual assessment begins, the patient will be able to perform tests to familiarize himself or herself with the procedure and will be allowed to rest at the end of each trial. The gait analysis will be quantified in terms of spatial–temporal parameters of the gait cycle, joint kinematics, and range of motion (ROM) of the lower limb joints (hip, knee, and ankle), joint dynamics in terms of moments and powers, and ground reaction forces (GRFs).

Only at T1, each patient of HuG will complete the Technology Acceptance Model questionnaire (TAM) [41], to assess technology acceptance.

#### Intervention group

HuG patients will undergo robotic treatment for the improvement of balance through the robotic platform (Hunova® Movendo Technology srl, Genova, IT), 3 times per week, each lasting 45 min, in addition to the conventional treatment. In particular, the technological rehabilitation performed employing a footboard will be mostly aimed at improving the balance both in sitting and standing positions and will be proposed static and dynamic exercises, dual-task exercises, and exercises to improve trunk control.

#### Control group

CoG patients will undergo conventional rehabilitation treatment only, using the main rehabilitation methods (e.g., neurocognitive theory, Bobath concept, progressive neuromuscular facilitation). Specifically, activities for improving balance, coordination, walking, and overall motor and cognitive performance will be carried out.

#### Criteria for discontinuation or modification of assigned interventions

The physical therapists involved in the study will modulate rehabilitation activities according to the patient’s individual tolerance. This tailoring of treatment will be done to avoid problems arising from pain or fatigue.

#### Strategies to improve adherence to interventions

Adherence to rehabilitation interventions will be monitored by the treating physical therapists for both HuG and CoG.

#### Relevant concomitant care permitted or prohibited during the trial

There are no restrictions on concomitant care.

#### Provisions for post-trial care

No assistance is provided at the end of the trial.

### Outcome

#### Primary outcome

The primary outcome for motor performance is the BBS value, both in HuG and CoG, at the end of the 4 weeks of treatment.

### Secondary outcomes

Balance, ambulation, and motor performance will be assessed through MI-LL, TUG, SPPB, AI, WHS, FAC, 10MWT, and 6MWT. Compared with T0, the change after 4 weeks in disability, perceived quality of life, and fatigue was assessed by BIM, EQ-5D, MFIS, and FSMC. Cognitive performance will be assessed by FAB, SCWT, SDMT, DCT, and TMT.

### Participant timeline

Table 2 shows the timeline of data collection.

**Table 2 Tab2:** Study plan and timing of procedures

Activity	Screening and enrolment	Week 0 (T0) Baseline	Week 4 (T1) Post-training
Token Test	X		
Signed informed consent	X		
Demographic and clinical data collection		X	
LTPAq		X	
CRIq		X	
MI-LL		X	X
BBS		X	X
TUG		X	X
SPPB		X	X
AI		X	X
WHS		X	X
FAC		X	X
10MWT		X	X
6MWT		X	X
Posturography (single-task and dual-task)		X	X
Gait analysis		X	X
BIM		X	X
EQ-5D		X	X
MFIS		X	X
FSMC		X	X
FAB		X	X
SCWT		X	X
SDMT		X	X
DCT		X	X
TMT		X	X
TAM			X

*LTPAq* Leisure Time Physical Activity questionnaire, *CRIq* Cognitive Reserve Index questionnaire, *MI-LL* Motricity Index Lower Limb, *BBS* Berg Balance Scale, *TUG* Timed Up & Go Test, *SPPB* Short Physical Performance Battery, *AI* Ambulation index, *WHS* Walking Handicap Scale, *FAC* Functional Ambulation Index, *10MWT* 10-Meter Walking Test, *6MWT* 6-Minute Walking Test, *BIM* Modified Barthel Index, *EQ-5D* Euro Quality of Life 5D, *MFIS* Modified Fatigue Impact Scale, *FSMC* Fatigue Scale for Motor and Cognitive Function, *FAB* Frontal Assessment Battery, *SCWT* Stroop Colour Word Test, *SDMT* Symbol Digit Modalities Test, *DCT* Digit Cancellation Test, *TMT* Trial making test, *TAM* Technology Acceptance Model questionnaire

### Sample size

Since this is a study of a specific subgroup of patients, on whom the actual utility of the Hunova® has not yet been studied in the literature, it is not necessary to formally estimate a minimum sample size. However, based on Julious’ rules [42], we estimate to enroll a sample of 24 subjects, randomized into two groups of equal size.

### Recruitment

Researchers, for eligibility, will evaluate all elderly people with stroke outcomes admitted to the post-acute rehabilitation unit.

### Assignment of interventions: allocation

Patients will be divided into two groups by randomization: one group will perform specific rehabilitation for balance disorder using the robotic platform (experimental group, HuG) in addition to conventional treatment, and the other group will perform only the conventional treatment (conventional group, CoG), as described later. The division into two groups will follow a randomization algorithm according to the procedure of random sorting. The allocation sequence will be generated through the PASS2019 software.

### Concealment method

The operator in charge of patient’s assessment will be blind to the allocation group, the operator applying the treatment will not be involved in the evaluation of patients, and a third operator will be responsible for generating the assignment sequence to the two groups.

### Implementation

After agreeing to participate, patients will be assigned an alphanumeric code to maintain data anonymity. The rehabilitation treatment physical therapist will be responsible for disclosing to the patient the group (HuG or CoG) to which they have been assigned.

### Assignment of interventions: blind

#### Who will be in the blinded

Blinding is limited to the researcher who will conduct the assessment and the researcher who will do the statistical analysis. Because of the visibility of the intervention, patients cannot be blinded.

#### Unblinding

Not applicable.

### Data collection and management

#### Plans for assessment and collection of outcomes

Researchers will collect data at the beginning and end of the 4-week treatment period. In addition, researchers will be trained in the administration of clinical scales.

#### Plans to promote participant retention and complete follow-up

In this study, there is no follow-up period after the end of the treatment period. In case participants discontinue the study, only data on the reason for discontinuation will be kept.

#### Data management

The study data will be collected and managed using the REDCap (Research Electronic Data Capture) electronic data capture tools [43, 44]. REDCap is a secure, Web-based software platform designed to support data capture for research studies by providing:An intuitive interface for validated data captureAudit trails for monitoring data manipulation and export proceduresAutomated export procedures for downloading data into common statistical packagesProcedures for data integration and interoperability with external sources

Only persons officially registered as experimenters or data managers will receive a user login to access the REDCap web platform and enter/manage data.

#### Confidentiality

Participants will be assigned an alphanumeric identification code, and participant data will be stored on secure servers in accordance with national laws. It is planned to set up an operational database in which to enter information, drawn from the assessment protocol, deemed to be of priority importance. Data will be accessible only to investigators participating in the trial.

#### Plans for collection, laboratory evaluation, and storage of biological specimens for genetic or molecular analysis in this trial/future use

Not applicable.

### Statistical methods

#### Statistical methods for primary and secondary outcomes

The sample will be described in its clinical and demographic variables through techniques of descriptive statistics. The normality of the quantitative data will be checked with the Shapiro–Wilk test. Normally distributed quantitative variables will be summarized with the mean and standard deviation (SD) or the median and interquartile range (IQR), otherwise. Qualitative variables will be presented through absolute and percentage frequency tables. The primary objective, i.e., assessment of balance as measured by the increase in values of the BBS between start and end of treatment in the two groups, will be assessed employing an ANCOVA model, where the BBS value at baseline will be shown as a covariate, the BBS at the end of treatment as a dependent variable, and the treatment as a factor. The variations of the different parameters between the two groups at individual time instants will be evaluated, concerning the qualitative variables, by Fisher’s exact test or chi-square test, with Yates correction, where appropriate. Quantitative variables will instead be analyzed utilizing the Student’s *t*-test, in case of normally distributed data, or with the Mann–Whitney *U* test, in the opposite case. The assessment, among secondary endpoints, of fatigue, motor and cognitive performance, quality of life, ambulation quality of life, gait, and balance, and cognitive-motor interference will also be assessed through ANCOVA models, as previously indicated for the primary endpoint. Values of *P* < 0.05 will be considered statistically significant. All analyses will be conducted with R software version 4.1.1. (CRAN ®) and STATA version 16 (STATA Corp).

#### Interim analysis

No interim analysis is provided.

#### Methods for additional analysis

No additional analysis is provided.

#### Methods in analysis to handle protocol non-adherence and any statistical methods to handle missing data

Non-inferiority will be tested using two sets of analyses: the intention-to-treat set, which considers all patients as randomized regardless of whether they received the randomized treatment, and the “per-protocol” set of analyses. Missing values, all < 10%, were treated by *imputeR* package, within R Software version 4.2.0 (CRAN®, R Core 2022, Vienna, Australia) [45], using multiple imputation with Lasso Regression methods centered on the mean as for quantitative data, while classification trees for imputation by “rpartC” function, centered on the mode, i.e., most represented class object, were applied on qualitative data [46].

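### The trial is labelled non-inferiority and says it will test it, but its hypothesis, its add-on comparison and its only decision rule are those of a superiority trial

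*Protocol article*

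**What the plan says.** Two places in the protocol article commit the trial to non-inferiority. Under Trial design it is an "interventional, single-blinded, non-inferiority, randomized control pilot trial". Under the heading on non-adherence and missing data, "Non-inferiority will be tested using two sets of analyses", namely intention-to-treat and per-protocol.

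Other places describe something else:

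- **Design statement in the abstract.** "This is an interventional, single-blinded, preliminary randomized control trial", with no mention of non-inferiority.
- **Hypothesis.** Background and rationale proposes that "robotic-assisted balance treatment associated with physical therapy may be more effective than usual therapy performed by a physical therapist". The abstract's background says the same in substance.
- **Comparison.** Study setting, Intervention group and Control group describe 12 robotic sessions of 45 minutes given on top of conventional treatment, against conventional treatment only.
- **Primary analysis.** The change in BBS "will be assessed employing an ANCOVA model, where the BBS value at baseline will be shown as a covariate", with end-of-treatment BBS as dependent variable, treatment as factor, and significance declared at P < 0.05.
- **Sample size.** The article holds that "it is not necessary to formally estimate a minimum sample size" and takes 24 patients in two equal groups from a published rule of thumb for pilot studies.

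**The concern.** A non-inferiority test and a superiority test have different null hypotheses. The first needs a margin and a rule for one confidence bound. The second asks whether the difference is zero. The article promises the first and specifies only the second, so a reader cannot tell what result would count as success on the primary outcome.

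Non-inferiority also does not fit the comparison. One group receives everything the other receives, plus extra sessions. The article names no offsetting advantage, such as replaced sessions or less therapist time, that would make a finding of no worse than conventional treatment useful. It would not answer the stated question of whether the addition brings benefit.

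The role of the analysis sets is affected too. Placing intention-to-treat and per-protocol side by side is a non-inferiority convention. For superiority, all randomised patients should lead.

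**Working it through.** **Step 1. Set the elements side by side.**

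| Element | Where | Framework it belongs to |
|---|---|---|
| Design label | Trial design | Non-inferiority |
| Test and analysis sets | Non-adherence and missing data | Non-inferiority |
| Design label | Abstract, Methods | Neither named |
| Hypothesis | Abstract; Background and rationale | Superiority |
| Groups compared | Study setting; Intervention group; Control group | Add-on, so superiority |
| Decision rule | Statistical methods for primary and secondary outcomes | Test of no difference |
| Margin or bound rule | None in the text at hand | – |

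Nothing in the article reconciles the first two rows with the rows on hypothesis, comparison and decision rule.

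**Step 2. The plan's own figure.** 24/2 = 12 per group, which is consistent. The article states no power, effect size, SD or margin, so there is no further calculation to reproduce.

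**Step 3. What 12 per group can exclude.** The article gives no SD for BBS, so results are in SD units. The correlation r between baseline and week-4 BBS is not given either, so it is assumed over a range. Complete data on all 24 patients and a two-sided 5% level are also assumed; the article does not state sidedness.

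Half-width h = t(0.975, df) × √[(1 − r²) × 2/12], with df = 22 unadjusted and 21 for ANCOVA with one covariate.

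- Unadjusted: 2.074 × √(0.1667) = 2.074 × 0.408 = 0.85 SD
- r = 0.5: 2.080 × √(0.75 × 0.1667) = 2.080 × 0.354 = 0.735, or 0.74 SD
- r = 0.7: 2.080 × √(0.51 × 0.1667) = 2.080 × 0.292 = 0.61 SD
- r = 0.8: 2.080 × √(0.36 × 0.1667) = 2.080 × 0.245 = 0.51 SD

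With an observed difference of zero, the lower limit lies at −h. A deficit of roughly half an SD or more in the robotic group would then remain compatible with the data in every row.

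**Step 4. How often the printed rule misses a real deficit.** Suppose the robotic group were truly 0.5 SD worse (an illustrative value). The chance that the ANCOVA treatment term is non-significant, from the noncentral t distribution with 21 df, is:

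| r | P(non-significant) |
|---|---|
| 0 | 0.785 |
| 0.5 | 0.729 |
| 0.7 | 0.627 |
| 0.8 | 0.505 |

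So absence of significance says little about whether the robotic group is worse, and P < 0.05 cannot stand in for a non-inferiority criterion.

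**The case against.** Several points can fairly be made for the plan.

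- **The test is not impossible.** The ANCOVA yields an adjusted difference and a confidence interval, the usual vehicle for non-inferiority. Only a margin and a bound rule are lacking, and this is a journal article that refers to a full protocol not shown here. This stands. A reader might infer that no margin exists or that the test cannot be done, but the documents support only the statement that none appears in the text at hand. A margin elsewhere would still not remove the conflict with the hypothesis, the add-on comparison and the P < 0.05 rule printed here.
- **No misuse is announced.** A reader might infer that the investigators intend to read P > 0.05 as non-inferior, and so as success. No section says so, and the Discussion frames the aim as evaluating improvement. The misreading is a possibility to be closed off, not a stated plan.
- **It is a pilot.** The article openly declines a formal sample size. This stands: the calculation above does not show that 24 is wrong, and a power shortfall is not the point because no power is claimed.
- **The label could be the intended one.** It appears twice, so non-inferiority may be what was meant. The hypothesis, groups and decision rule all point the other way. If non-inferiority really is meant, the plan would need a justified BBS margin, a bound rule and a matching sample size, as well as a different stated hypothesis.
- **The primary estimate would be the same after relabelling.** This is true of the ANCOVA model. What changes is the null hypothesis, the reading of the result and the standing of the per-protocol set.

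**Conclusion.** The concern holds as a contradiction within the article. Non-inferiority is declared in two sections, one of them statistical, while the hypothesis, the comparison and the only decision rule belong to a superiority or difference trial. This conclusion rests on the printed text alone and does not depend on what an unshown document may add.

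The size of the consequence rests on assumptions. With 12 per group and complete data, the expected 95% half-width is about 0.85 SD unadjusted and 0.74, 0.61 or 0.51 SD at assumed correlations of 0.5, 0.7 or 0.8. Non-significance would therefore not in itself rule out a sizeable deficit.

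**What to change.** - Remove the non-inferiority wording from Trial design and from the section on non-adherence and missing data.
- State one two-sided superiority comparison of BBS at 4 weeks, using the ANCOVA already described. Report the adjusted difference with its 95% confidence interval as a preliminary estimate.
- Make the intention-to-treat set, meaning all randomised patients, primary and the per-protocol set a sensitivity analysis.
- Reconcile that set with the section on participant retention, under which only the reason is kept for participants who discontinue. Read literally, this leaves no outcome data for patients whom the intention-to-treat analysis must include.
- State that P > 0.05 will not be taken as evidence of non-inferiority or equivalence.

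The cost is a wording amendment and the loss of a non-inferiority claim. The article reserves important changes for ethics committee authorisation, and this one may qualify. Patients, visits and treatments do not change. Enrolment was ongoing when the article was published, so the amendment should be made before outcome data are analysed.

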## Trial status

Protocol version 2, 7 December 2021. Initiation of recruitment of patients by February 2022. Enrollment is still ongoing. https://clinicaltrials.gov/ct2/show/NCT05280587?term=NCT05280587&draw=2&rank=1

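### The missing-data paragraph states a result (all below 10%) while patients are still being enrolled, and its so-called multiple imputation reads, as worded, as mean or mode filling that carries no imputation uncertainty into the ANCOVA

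*Protocol article*

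**What the plan says.** The section on non-adherence and missing data reports "Missing values, all < 10%, were treated by *imputeR* package". For quantitative variables it describes "using multiple imputation with Lasso Regression methods centered on the mean as for quantitative data". For qualitative variables it describes classification trees that supply the most frequent class. The same paragraph defines the intention-to-treat and per-protocol sets for a non-inferiority test.

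Other sections bear on this:

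- Trial status: "Enrollment is still ongoing".
- Interim analysis: none is planned.
- Sample size: "we estimate to enroll a sample of 24 subjects, randomized into two groups of equal size".
- Statistical methods: the primary analysis is an ANCOVA "where the BBS value at baseline will be shown as a covariate, the BBS at the end of treatment as a dependent variable", with treatment as a factor. "Values of *P* < 0.05 will be considered statistically significant".
- Participant retention: for a patient who discontinues, only the reason for stopping is retained.

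**The concern.** There are two faults, and both lie in what the text states rather than in what it leaves out.

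First, a share of missing values is given as an established fact before the data can exist in final form. A reader learns what was supposedly found, but not what will be done if 10% is reached or passed.

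Second, the label and the description disagree. Multiple imputation replaces each gap with several random draws and adds the spread between them to the standard error. A prediction centred on the mean, or the commonest class, is a single central value. If such values enter the ANCOVA as though observed, one of two things happens. With arm in the fill model, the standard error is too small and the test rejects too often. Without arm, the two groups are pulled together. Under the non-inferiority framing, that pull favours the non-inferiority conclusion if the experimental arm is truly worse, and a standard error that is too small makes the interval too narrow.

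**Working it through.** **Inputs from the document.** N = 24, 12 per arm; significance level 0.05 (taken as two-sided, since the text does not say); ANCOVA of end-of-treatment BBS on baseline BBS and arm; missingness stated as below 10%.

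**Inputs assumed, because the document gives none.** SD 1; correlation between baseline and end-of-treatment BBS 0.7; values lost completely at random; ordinary regression fill standing in for the Lasso.

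**Step 1: what the bound allows.** 10% of 24 is 2.4, so at most two missing values. 1/24 = 4.2%, 2/24 = 8.3%, 3/24 = 12.5%. The stated figure cannot be reproduced, because no data are given.

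**Step 2: fill with arm in the model.** Filled points lie exactly on the fitted plane. The treatment estimate is therefore the same as from observed cases, and the residual sum of squares does not change. The analysis nevertheless counts N patients instead of the o observed. Relative to the observed-case analysis, the standard error is multiplied by about

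f = sqrt((o − 3)/(N − 3)) × sqrt(o/N).

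The nominal cut-off is t on 21 df = 2.080. The true type I error is about P(|t| on o − 3 df > 2.080 × f). The correlation does not enter this formula.

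- 1 missing: f = sqrt(20/21) × sqrt(23/24) = 0.955; cut-off 1.987 on 20 df; type I error 6.1%.
- 2 missing: f = sqrt(19/21) × sqrt(22/24) = 0.911; cut-off 1.894 on 19 df; type I error 7.4%.
- 4 missing (outside the bound): f = sqrt(17/21) × sqrt(20/24) = 0.821; cut-off 1.708 on 17 df; type I error 10.6%.

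Simulation with 20,000 runs agrees: 6.0% with 1 missing and 7.4% with 2. With 2 missing, the mean model standard error is 0.281 against a true SD of 0.314 (ratio 0.89), and coverage is 92.6%. Separate simulations with 4 missing gave 10.6 to 10.8%.

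**Step 3: fill without arm.** The effect is multiplied by roughly o/N: 23/24 = 0.958, 22/24 = 0.917, 20/24 = 0.833. Simulated factors are 0.951 with 1 missing and 0.910 with 2. With 4 missing, a true effect of 0.80 SD is estimated as about 0.66, and 0.66/0.80 = 0.825, a loss of about 18%. In the 20,000-run simulation (1, 2 or 5 missing), type I error stays near 5%.

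**Step 4: comparator.** ANCOVA on observed values with 2 missing gives an effect factor of 1.00, type I error 4.9% and coverage 95.0%. Proper multiple imputation was not simulated.

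**Step 5: patients who discontinue.** The intention-to-treat set includes everyone randomised. The retention section keeps only the reason for stopping. Taken literally, a patient who drops out has no baseline BBS left to impute from or adjust for, so the two statements cannot both be carried out.

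**The case against.** The strongest reply is that the text is ambiguous rather than plainly wrong. It uses the term multiple imputation and is silent on draws, number of data sets and pooling, which a statistical analysis plan may supply. That is fair: the absence of draws and pooling is inferred from the description of central values, and the document does not state it. Nor does it state whether arm is in the fill model, so neither consequence can be singled out. What remains is that the description given does not match the label.

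A reader might infer that the past tense shows someone had already looked at trial data, or that the paragraph came from another study. The document supports neither. No interim analysis is planned, and the Secondary outcomes section also slips into the past tense for future work, so a drafting slip is just as plausible.

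A reader might also quote the figures near 11%. They require 4 of 24 missing (16.7%), which is outside the document's own bound.

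The simulated model is also somewhat unfavourable. The plan collects many other end-of-treatment measures. Adding one assumed auxiliary predictor (correlation 0.7 to 0.85 with end-of-treatment BBS), with 2 missing, brings type I error to 6.7 to 5.9% with arm in the model. Without arm, a 0.80 SD effect is then estimated as 0.75 to 0.78. This reduces the size of the problem but does not remove it.

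Finally, this is a pilot for which the authors hold that "it is not necessary to formally estimate a minimum sample size". That bears on severity. It does not excuse a rule that cannot be applied as written.

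**Conclusion.** The point holds in two parts. The claim of less than 10% missing is a result where a rule is needed, and it fails with the third missing value. The imputation, as worded, is deterministic filling under the name of multiple imputation.

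Within the stated bound the distortion is modest: type I error of about 6 to 7% with arm in the fill model, or an effect 5 to 9% too small without it. It is smaller with strong auxiliary predictors and larger if missingness exceeds 10%. These sizes rest on completely random loss and a plain regression fill, neither of which comes from the document. The assumed correlation of 0.7 hardly matters for the type I error, since it drops out of the approximation in Step 2. That the imputation is in fact single-valued is a reading of the wording and is not established. Severity: should be fixed before analysis.

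**What to change.** 1. Delete the below-10% statement and rewrite the paragraph in the future tense, as a rule that applies at any level of missingness.
2. For end-of-treatment outcomes, replace mean and mode filling with one of two options: baseline-adjusted ANCOVA on observed values under a stated missing-at-random assumption, or proper multiple imputation with random draws, arm and baseline outcome always in the model, and pooling by Rubin's rules.
3. Reconcile the retention section with the intention-to-treat set by keeping the data already collected on patients who discontinue. Without this, neither the imputation nor a sensitivity analysis has anything to work from for those patients.

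A delta-shift sensitivity analysis for BBS and a fixed minimum number of imputations are optional. The R version should also be made consistent (4.1.1 in the statistical methods, 4.2.0 in the missing-data section).

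The cost is some rewording and a few lines of code. The confidence interval becomes slightly wider: with 2 missing, the mean model standard error is 0.310 from observed-data ANCOVA against 0.281 from the fill with arm. Treatment and assessments do not change.
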